**Table 2 Tab2:**
[figure not shown]
Data collection tool: prostate cancer PtDA implementation study

A survey will be sent to urologists (*n* = 8–10) per site, radiation oncologists (*n* = 5-7), and nurses (*n* = 4–6) in the prostate programs to assess their use of PtDA and factors influencing use. Eligible participants will receive a mailed package that will include a cover letter with the study purpose and information on how the information will be used and the survey with a stamped pre-addressed envelope. To enhance response rates, Dillman’s approach will be used with reminders at 2, 4, and 5 weeks [39].

Interviews will be conducted with a purposeful sample of men given/not given the PtDA (and/or their partners), nurses, managers, radiation oncologists, and urologists in each program (Table 1). Men newly diagnosed with prostate cancer during the last 3 years post-PtDA implementation will be contacted by a healthcare professional from the circle of care or through the local prostate cancer support groups. Purposeful sampling will be used to identify other stakeholders having varying levels of influence in the prostate cancer programs (e.g., nurses, urologists, radiation oncologists, and managers). Prospective participants will be invited to participate in an interview by (a) announcement of the study at staff meetings, (b) hard copy posters on staff bulletin boards, and (c) email to staff (Ottawa only). A letter explaining the study will be provided to prospective participants, and written informed consent will be obtained (Additional files 1 and 2). For healthcare practitioners, a semi-structured interview guide developed using the Knowledge to Action Framework [35] will be used to explore perceptions of PtDAs, factors influencing PtDA sustained use, interventions required to overcome remaining barriers, and concurrent initiatives that may have influenced PtDA use. For men given or not given a PtDA, a semi-structured interview guide was developed to learn more about their experience with how the decision was made to treat or monitor their prostate cancer. All participants will be asked to complete demographic questions.

*Interventions* will be identified to address barriers interfering with the use of PtDAs if the prevalence of use is found to be less than 80 %. If PtDA use is 80 % or higher, strategies for monitoring sustained use with feedback mechanisms will be established [40]. Successful implementation of evidence in clinical practice requires tailored interventions based on identified barriers [41].

*Instruments* to be used have been found to be valid, reliable, and have been previously been used in PtDA studies. The four-item SURE test is used to screen for decisional conflict to inform clinical practice [42–44]. It has moderate reliability (Cronbach Alpha 0.65) and discriminates between those who had/had not made a choice. Factors influencing PtDA use by practitioners will be measured using the 12-item Continuing Professional Development Reaction Questionnaire (Cronbach Alpha 0.77-0.85) [45]. Potential environmental barriers influencing PtDA use will be taken from a Barriers Survey [46].

*Outcomes* are based on the Knowledge to Action Framework [35]. After knowledge is implemented (e.g., PtDA), its uptake should be monitored to determine how and to what extent it is used [35]. We plan to use administrative data to measure the proportion of men who were given the PtDA and qualitative interviews to explore men’s use. The next phase of the Framework is to measure the impact of knowledge use on outcomes specific to patients, providers, and healthcare systems [35]. We will measure the impact of PtDA use on men’s decisional conflict using administrative data; practitioners’ and patients’ consultations using qualitative interviews; and impact on healthcare systems using administrative data to measure uptake of treatment and types of practitioners consulted during decision-making. Measuring impact of PtDA on these outcomes will ensure that PtDA use is influencing quality indicators as observed in randomized controlled trials without any unintended consequences [13, 40]. Sustaining the use of the knowledge is the last phase in the Action Cycle of this Framework [35, 47]. Given that barriers can change with PtDA use [46], we will assess barriers using a practitioner survey and qualitative interviews.

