**Methods/design:**

Guided by the Knowledge to Action Framework, this comparative case study will be conducted using administrative data, interviews, and surveys. Cases will be bound by geographic location (one hospital in Ontario; province of Saskatchewan) and time. Eligible participants will be all men newly diagnosed with localized prostate cancer, with outcomes assessed using administrative data and interviews. Nurses, urologists, radiation oncologists, and managers will be surveyed and a smaller sample interviewed. Cases will be established for each setting with findings compared across cases. Changes in the proportions of men given the PtDA over 2 years will be determined from administrative data. Factors associated with receiving the PtDA will be explored using multivariable logistic regression analysis. To assess the impact of the PtDA, outcomes will be described using mean and standard deviation (men’s decisional conflict) and frequency and proportions (practitioners consulted, uptake of treatment). To estimate the effect of the PtDA on these outcomes, adjusted mean differences and odds ratios will be calculated using exploratory multivariable general linear regression and binary or multinomial logistic regression. Factors influencing sustained PtDA use will be assessed using descriptive analysis of survey findings and thematic analysis of interview transcripts.

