*Procedures* focus on collecting clinical administrative data (clinical databases, electronic/paper-based health records) and conducting a survey and interviews (Table 1). Routinely collected administrative data sources will be reviewed to identify men newly diagnosed with localized prostate cancer for calendar years of 2011–2012 in Ottawa and 2014–2015 in Saskatchewan. Data will be retrieved on (a) their age, co-morbidities with severity, prostate cancer characteristics; (b) practitioners’ documentation of the decision-making consultation; (c) uptake of treatment or surveillance; (d) whether given the PtDA or not; and (e) level of decisional conflict (Table 2).

**Table 1 Tab1:** Proposed study data collection elements and analysis

Outcome	Participants	Data source	Analysis
Proportion given the PtDA	Men with localized prostate cancer	Clinical administrative^a^ data (~*n* = 1000)	Proportion with 95 % confidence intervals for each case study
Men’s outcomes: decisional conflict	Men with localized prostate cancer	Clinical administrative^a^ data (~*n* = 1000)	Linear regression (decisional conflict) to compare those who were given the PtDA to those who were not
Practitioner’s outcome: factors influencing PtDA use	Urologists, radiation oncologists, and nurses in prostate programs	Mailed survey (~*n* = 40)	Multivariable ordinal logistic regression analysis of practitioner’s reported use of PtDA with factors reported in the survey as covariates. Subgroup analysis will be done by types of practitioner (e.g., urologists, radiation oncologists, nurses)
Health system outcomes: uptake of treatment (including surveillance) and practitioner consultations	All men with localized prostate cancer	Clinical administrative^a^ data (~*n* = 1000)	Multinomial and binary logistic regression analysis of treatment uptake and practitioner consultations with receipt of the PtDA as main predictor, and adjusting for patient demographic and clinical characteristics.
Factors influencing PtDA implementation	Key stakeholders in each program	Individual interviews (~*n* = 30–40)	Thematic analysis guided by the Knowledge to Action Framework

^a^Clinical administrative data for all men for 2-year period after implementing the PtDA

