Outcomes between those given the PtDA and those not given it will be described at each site using mean and standard deviation (decisional conflict) and frequency and proportions (uptake of treatment, type of practitioner consulted). To estimate the effect of the PtDA on these outcomes after accounting for potential confounders, we will conduct exploratory multivariable general linear regression and binary or multinomial logistic regression at each site and overall. The analysis will adjust for patient characteristics associated with the use of the PtDA, and patient clinical and demographic characteristics potentially associated with the outcomes. To explore differences between the sites, we will include site and its interaction with the receipt of the PtDA into the model. Results will be expressed as adjusted mean differences and adjusted odds ratios together with 95 % confidence intervals.

For impact on practitioner outcomes and sustained use, we will identify remaining barriers influencing practitioner PtDA use with the survey and interview data. Audio-taped interviews will be transcribed verbatim and analyzed qualitatively by two team members using thematic analysis. We expect to reach saturation by 12 to 15 interviews in each case study [48].

The study *Timeline* is 12 months: 3 months for start-up; 5 months for collecting clinical administrative data, conducting the survey, and interviewing; 2 months for data cleaning/analysis; and 2 months for drafting case studies and disseminating findings.

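### Decisional conflict is measured with a four-item screen but reported only as a mean difference: add the proportion screening positive and use robust standard errors

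*Protocol article*

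**What the plan says.** Methods/design, Instruments paragraph: "The four-item SURE test is used to screen for decisional conflict to inform clinical practice". The next sentence adds: "It has moderate reliability (Cronbach Alpha 0.65) and discriminates between those who had/had not made a choice". No other measure of decisional conflict is named. The Procedures paragraph lists, among the items drawn from administrative records, the "level of decisional conflict (Table 2"; Table 2 itself is not shown.

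The summary and the model are fixed in three places:

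- Abstract, Methods/design: "outcomes will be described using mean and standard deviation (men’s decisional conflict) and frequency and proportions (practitioners consulted, uptake of treatment".
- Table 1, the row for men's outcomes: "Linear regression (decisional conflict) to compare those who were given the PtDA to those who were not".
- Analysis section: groups are described "using mean and standard deviation (decisional conflict) and frequency and proportions (uptake of treatment, type of practitioner consulted".

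The Analysis section then says that results will be given as adjusted mean differences and adjusted odds ratios with 95% confidence intervals, at each site and overall. The odds ratios belong to other outcomes, because Table 1 assigns "Multinomial and binary logistic regression analysis of treatment uptake and practitioner consultations with receipt of the PtDA as main predictor". No cut-off, proportion screening positive, or binary or ordinal model is stated for decisional conflict.

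**The concern.** A four-item screen yields a score with few possible values. Its usual product is a classification: conflict detected or not. The plan handles the score as a continuous scale. Two things follow.

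First, a difference in means does not determine the difference in the share of men who screen positive. The Background section explains why decisional conflict matters by describing the consequences for adults in whom it stays unresolved, so readers will want that share. The Outcomes paragraph also wants to rule out unintended effects, and a rise in the number of men left with some conflict could sit behind an improved mean.

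Second, ordinary linear-regression standard errors assume the same variance in both groups. On a bounded score the variance usually shrinks as the mean approaches the limit. Where the group with the larger variance is also much the smaller, the pooled interval is too narrow. Site-specific models are planned, and the Saskatchewan split is very uneven.

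**Working it through.** **Inputs from the Analysis section.** About 600 men in Ottawa with 50% given the aid, and about 400 in Saskatchewan with 90% given it. Not given: 600 × 0.50 = 300 in Ottawa; 400 × 0.10 = 40 in Saskatchewan. Given: 300 and 360.

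**The plan's own figures.** The article gives no sample size, effect size or SD for decisional conflict. Its nearest figures are the margins of error for the proportion given the aid, 1.96 × √(p(1−p)/n):

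- Ottawa: 1.96 × √(0.25/600) = 4.00 points (stated 4.0).
- Saskatchewan: 1.96 × √(0.09/400) = 2.94 points (stated 2.9).

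Both reproduce, and nothing below changes them.

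**Assumptions not in the documents.** Four yes/no items summed to 0–4, with a higher score better; conflict present if the score is below 4 (alternative: below 3). Distributions are listed as percentages at scores 0/1/2/3/4.

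**Check 1: what a mean difference leaves open.** Not-given group 5/5/10/20/60: mean = 0.05 + 0.20 + 0.60 + 2.40 = 3.25, SD 1.13, 40% below 4, 20% below 3. Three given groups all have mean 3.45, a difference of +0.20:

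| Given group | SD | Below 4 | Below 3 |
|---|---|---|---|
| 5/5/10/0/80 | 1.16 | 20% | 20% |
| 0/0/15/25/60 | 0.74 | 40% | 15% |
| 0/0/0/55/45 | 0.50 | 55% | 0% |

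The limits at mean 3.45 are these. The largest share at 4 is 3.45/4 = 86.25%, leaving 14% below. The smallest solves 3 + p = 3.45, so p = 45%, leaving 55% below. The third row is therefore a boundary case.

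**Check 2: interval coverage.** This compares two means, without covariates or clustering. Pooled variance s² = [(n₀−1)v₀ + (n₁−1)v₁]/(n₀+n₁−2). The SE the model reports is √(s²(1/n₀+1/n₁)); the true SE is √(v₀/n₀ + v₁/n₁). Approximate coverage is 2Φ(1.96 × reported/true) − 1. The not-given group is as above, v₀ = 1.2875.

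Worked case, Saskatchewan, given 2/2/5/11/80 (mean 3.65, v₁ = 0.6875):

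- s² = (39 × 1.2875 + 359 × 0.6875)/398 = 0.746.
- Reported SE = √(0.746 × (1/40 + 1/360)) = 0.144.
- True SE = √(1.2875/40 + 0.6875/360) = 0.185.
- 1.96 × 0.1440/0.1847 = 1.53, so coverage is about 87%.

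| Given group | v₁ | Reported SE | True SE | Coverage, 40 vs 360 |
|---|---|---|---|---|
| 5/5/10/20/60 (no difference) | 1.2875 | 0.189 | 0.189 | 95% |
| 3/3/6/13/75 | 0.908 | 0.162 | 0.186 | 91% |
| 2/2/5/11/80 | 0.6875 | 0.144 | 0.185 | 87% |
| 1/1/3/10/85 | 0.417 | 0.118 | 0.183 | 80% |

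Simulation agreed to within about half a percentage point, and unequal-variance intervals covered about 94% throughout. At 300 versus 300 the reported and true SEs are equal whatever the variances, so coverage is 95% in every row.

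The loss depends on the shape. If 85% score 4 and the lower scores shrink in proportion (1.875/1.875/3.75/7.5/85, v₁ = 0.615), the SEs are 0.1375 and 0.184 and coverage is about 86%.

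**The case against.** The strongest reply is that the objective asks about the impact on decisional conflict, and the records supply its level. A difference in mean level answers that, and the plan nowhere promises a count of men with conflict. The regressions are labelled exploratory, and no sample size rests on this outcome. The scoring rule and cut-off are not in the article, so the illustrations rest on assumptions. SDs will be shown by group, so a large change of shape would be partly visible. The article is condensed, and extra summaries and the choice of standard error could sit in an unseen analysis plan.

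Much of this stands. A reader might infer that linear regression is invalid here, or that the plan fails its objective; the documents support neither. Nor does the reliability of 0.65 favour one model over another, since a dichotomised score carries the same measurement error. A logistic model would rest on the same 40 or so men. Whether the linear or the ordinal result should lead is a matter of preference.

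Two points remain. The mean, SD and linear model are positively stated, and proportions and logistic models are expressly allotted to other outcomes, so this is a stated choice and not merely an omitted detail. And an SD beside a mean still does not give the share screening positive.

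**Conclusion.** The concern holds as a mismatch between a screening instrument and a reporting plan confined to means. It is not a wrong number or an invalid analysis. The planned mean difference is estimable and meaningful as a difference in score. It leaves the share screening positive undetermined: 14% to 55% below the maximum for one mean difference of +0.20 from a 40% baseline. Separately, constant-variance intervals can cover about 80–91% instead of 95% in Saskatchewan when the aid raises scores towards the limit. They are sound there when there is no difference, and sound at Ottawa's 300 versus 300.

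This rests on a 0–4 score, on illustrative distributions, on the expected 90% receipt in Saskatchewan, on ordinary standard errors being used (the article does not say otherwise), and on the recorded level of conflict being the SURE result, inferred because no other instrument is named. Were the smaller group the less variable one, the pooled interval would be too wide instead.

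**What to change.** 1. Keep the adjusted mean difference, but base its 95% confidence interval on robust (unequal-variance) standard errors.
2. State the score range and the instrument's own cut-off. Report the full score distribution and the number and proportion screening positive, by receipt of the decision aid and by site.
3. Alongside the mean difference, add an adjusted ordinal logistic comparison of the score (or a binary one of screen-positive status) with a 95% confidence interval. Table 1 already plans ordinal logistic regression for practitioners' reported use, so the method is familiar to the team.

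The cost is a little more analysis on the same data, with no new collection. Any dichotomised version loses some information, which the ordinal model avoids. With about 40 men not given the aid in Saskatchewan, the added site-specific comparison will be imprecise there and should be read accordingly.

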### Analysis

Two cases will be developed with a rich description of the context and outcomes with comparisons within and across the cases [37]. For PtDA use, the proportion of men given the PtDA will be calculated for each site with 95 % confidence intervals (Table 1). We anticipate about 600 men diagnosed with localized prostate cancer over 2 years at The Ottawa Hospital Cancer Assessment Clinic and 400 in the Provincial Prostate Pathway in Saskatchewan. Using conservative estimates for proportions given the PtDA of 50 and 90 % in Ottawa and Saskatchewan, respectively, these sample sizes are adequate to estimate the true proportions given the PtDA with margins of error +4.0 % in Ottawa and +2.9 % in Saskatchewan using two-sided 95 % confidence intervals. Characteristics and outcomes of patients who did and did not receive the PtDA will be described at each site using mean and standard deviation for continuous variables, and frequencies and proportions for categorical variables.

Factors associated with receiving the PtDA will be explored at each site and overall using multivariable logistic regression analysis by entering patient characteristics (e.g., age, co-morbidity, severity of disease, cancer characteristics) as well as provider characteristics (e.g., sex, years of experience, discipline). To explore differences in the effect of these characteristics across the two sites, site and interactions between the characteristics and site will be included in the model. If the proportion using the PtDA is 50 % in Ottawa and 90 % in Saskatchewan, according to a commonly used rule of 10 events per independent variable, the maximum number of variables that can be included in these analyses is 66; thus, we have more than the required degrees of freedom available to fit our models. The extent of missing data will be tabulated, and characteristics of those with and without missing data will be compared. If more than 5 % missing data is observed among predictors, the use of multiple imputation will be explored. The analysis will account for clustering by provider through the inclusion of random intercepts for each provider. The model will be estimated using pseudo-likelihood or maximum likelihood in SAS v9.3.

Outcomes between those given the PtDA and those not given it will be described at each site using mean and standard deviation (decisional conflict) and frequency and proportions (uptake of treatment, type of practitioner consulted). To estimate the effect of the PtDA on these outcomes after accounting for potential confounders, we will conduct exploratory multivariable general linear regression and binary or multinomial logistic regression at each site and overall. The analysis will adjust for patient characteristics associated with the use of the PtDA, and patient clinical and demographic characteristics potentially associated with the outcomes. To explore differences between the sites, we will include site and its interaction with the receipt of the PtDA into the model. Results will be expressed as adjusted mean differences and adjusted odds ratios together with 95 % confidence intervals.

For impact on practitioner outcomes and sustained use, we will identify remaining barriers influencing practitioner PtDA use with the survey and interview data. Audio-taped interviews will be transcribed verbatim and analyzed qualitatively by two team members using thematic analysis. We expect to reach saturation by 12 to 15 interviews in each case study [48].

The study *Timeline* is 12 months: 3 months for start-up; 5 months for collecting clinical administrative data, conducting the survey, and interviewing; 2 months for data cleaning/analysis; and 2 months for drafting case studies and disseminating findings.

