The overall aim of this comparative case study is to evaluate two strategies for implementing PtDAs in clinical pathways for men with localized prostate cancer by measuring (a) the use of PtDA over a 2-year period after implementation; (b) impact of the PtDA on men, practitioners, and health system outcomes; and (c) factors influencing sustained use (or not) for each strategy.

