## Methods/design

Our comparative case study will use mixed methods and will be guided by the Knowledge to Action Framework [35, 36]. Following Yin’s approach, the cases will be bound by location (prostate cancer clinical pathway at one hospital in one provincial health system and the prostate cancer surgical pathway in another province) and time period (2 years after PtDA implementation) [37]. The Knowledge to Action framework focuses on specific implementation factors essential for success in real world, naturalistic environments [35, 36]. The Action Cycle was activated by a problem identified by the knowledge users (e.g., men want to be more involved in prostate cancer decisions), and the knowledge solution is a PtDA. Then, we will identify interventions to overcome identified barriers. This proposed implementation study is focused on the final phases of the Framework: monitor use, evaluate outcomes, and measure sustained use. Sustainability requires monitoring use for 2 or more years [38]. We obtained ethics approval at The Ottawa Health Science Network Research Ethics Board (#20150604-01H), the Saskatoon Health Region Research Ethics Board (#BEH-15-382), Reginal Qu’Appelle Health Region Research Ethics Board (REG-15-125), and the University of Saskatchewan Behavioural Research Ethics Board (BEH#15-382).

The *setting* for our study is prostate cancer healthcare services that implemented PtDAs in the clinical pathways: The Ottawa Hospital in Ontario (in 2010) and the Ministry of Health in the Province of Saskatchewan (in 2013). These prostate cancer healthcare services have urologists and radiation oncologists serving populations of about 1 million each. Annually, about 400 men have consultations for prostate cancer at The Ottawa Hospital Cancer Assessment Clinic and about 600 in Saskatchewan. Within the clinical pathway, men diagnosed with localized prostate cancer are asked to use the PtDA at home in preparation for the consultation. Nurses, trained in interprofessional shared decision-making [31], discuss men’s questions prior to the physician consultation.

*Participants* for the interviews are men who have received a diagnosis of localized prostate cancer (including their partners) and received services at The Ottawa Hospital or in Saskatchewan. Other stakeholder participants who have varying levels of influence in the prostate cancer programs include urologists, radiation oncologists, nurses, and managers.

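### The abstract promises change in decision-aid use over two years, but the Analysis section and Table 1 plan one two-year proportion per site and no model names time

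*Protocol article*

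**What the plan says.** The Protocol article describes the analysis of use in two ways.

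**What is promised.** The abstract (Methods/design) states: "Changes in the proportions of men given the PtDA over 2 years will be determined from administrative data". Aim (a), at the end of the Background, is to measure "the use of PtDA over a 2-year period after implementation", and aim (c) is "factors influencing sustained use (or not) for each strategy". The opening of Methods/design places the study in the last phases of its framework, "monitor use, evaluate outcomes, and measure sustained use", and adds that sustainability calls for at least two years of monitoring.

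**What is planned.** The Analysis section says that "the proportion of men given the PtDA will be calculated for each site", with 95% confidence intervals. The matching row of Table 1 reads "Proportion with 95 % confidence intervals for each case study", and its footnote takes all men in the two-year period together. The model for receiving the PtDA enters patient characteristics, provider characteristics, site and interactions with site, with random intercepts for provider. The exploratory outcome models enter receipt, patient characteristics, site and the receipt-by-site interaction. Neither names calendar time or time since implementation. Sustained use is otherwise approached through barriers reported in the practitioner survey and the interviews.

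**What depends on it.** In the Interventions paragraph, interventions against barriers are identified "if the prevalence of use is found to be less than" 80%. At or above that level, strategies for monitoring sustained use are set up instead.

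**The concern.** A single proportion over two years is an average. It has the same value whether use was steady, rising or falling, so it cannot deliver the change that the abstract promises or measure whether use was sustained. The survey and interviews may bring a decline to light, but they cannot estimate its size. With no time term in the model for receipt, the regression does not fill the gap.

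Two smaller matters follow. The 80% rule speaks of use, while the Outcomes paragraph says that the administrative data measure men given the PtDA and leaves men's actual use to interviews. The rule also does not say which period its figure covers. Separately, if both PtDA distribution and treatment choice drifted over the window, the outcome models would have no term to absorb that drift.

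**Working it through.** **Inputs (Analysis section).** Ottawa: 600 men over two years, planning proportion 0.50, stated margin 4.0 points. Saskatchewan: 400 men, 0.90, 2.9 points. Intervals are two-sided 95%.

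**Step 1: reproduce the stated margins.** Half-width = 1.96 × √(p(1−p)/n).
- Ottawa, n = 600: 1.96 × √(0.25/600) = 4.0 points.
- Saskatchewan, n = 400: 1.96 × √(0.09/400) = 2.9 points.

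With half of each total, as a yearly estimate would have:
- Ottawa, n = 300: 1.96 × √(0.25/300) = 5.7 points.
- Saskatchewan, n = 200: 1.96 × √(0.09/200) = 4.2 points.

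Only the two-year totals match. The text does not use the word pooled, but that is what its precision statement describes.

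**Step 2: what the pooled figure hides.** Trajectories are illustrative, with an equal split by year.
- Ottawa, 60% then 40%: (60 + 40)/2 = 50%, interval 46.0 to 54.0%. Steady use at 50% gives the same result.
- Saskatchewan, 95% then 85%: (95 + 85)/2 = 90%, interval 87.1 to 92.9%. Steady use at 90% gives the same result.

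**Step 3: what the same data could show by year.** Half-width of the year 2 minus year 1 difference = 1.96 × √(2p(1−p)/n), with n per year.
- Ottawa: 1.96 × √(2 × 0.25/300) = 8.0 points.
- Saskatchewan: 1.96 × √(2 × 0.09/200) = 5.9 points.

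The change detectable with 80% power at two-sided 5% is about (1.96 + 0.84) × √(2p(1−p)/n), or 11.4 points in Ottawa and 8.4 in Saskatchewan. None of these figures allows for clustering by provider, which the plan itself models and which would widen them.

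**Step 4: does a decline change the 80% rule?** At Ottawa's planned 50%, the average is below 80% and so is the later part of any decline, so the branch is the same either way. At Saskatchewan's planned 90%, a linear decline cannot start above 100%, so it cannot end below 2 × 90 − 100 = 80%. The same bound holds for the second of two equal years. A linear fall from 95% to 69% would average (95 + 69)/2 = 82% and take the monitoring branch while ending below 80%, but that average is not one the plan assumes.

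**The case against.** The strongest reply is that the article is condensed. The abstract already commits to determining change, and the Analysis section promises comparisons within and across cases. It nowhere says that the two-year proportion is the only summary. The margin calculation may only justify sample size for the headline figure, and the choice between year, quarter and trend term could be left to a fuller plan. Aim (a), read literally, is answered by a two-year proportion, and aim (c) concerns factors, which the survey and interviews address.

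Much of this stands, and it limits the point. A reader might infer that a decline would certainly go unseen. The documents do not support that, because the intention to look at change is on record. What remains is that both places that specify the analysis of use, the Analysis text and Table 1, omit a stated undertaking and describe something else. That is an inconsistency within the document, not merely detail left out.

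A reader might also infer that the 80% rule would certify a decaying programme as sustained. The Interventions paragraph does not say this. Reaching 80% leads to monitoring, not to a verdict of sustained use, and the paragraph does not say that the two-year average feeds the rule. At the planning values a linear decline would not change the branch.

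Finally, confounding by calendar time is only a possibility. The documents give no figure for drift, and the outcome models are labelled exploratory.

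**Conclusion.** The point holds in a limited form. The Analysis section and Table 1 do not carry out the abstract's undertaking to determine change. As written, the quantitative analysis yields one pooled two-year proportion per site and cannot distinguish stable use from decline. A 20-point fall in Ottawa, from 60% to 40%, would leave the reported figure at 50%.

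The existing data can address this. Yearly margins are about 5.7 and 4.2 points, and margins for the between-year difference are about 8.0 and 5.9 points. That is enough for large declines and weak for small ones. These figures assume the planned proportions, an equal split of men between years and no clustering.

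The effect on the 80% rule is a matter of clarity: its measure and period are not stated. A late abrupt drop is not excluded by the linear argument above, but nothing in the documents suggests one.

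**What to change.** 1. In the Analysis section and Table 1, add the proportion given the PtDA at each site by year (or quarter) since implementation, with 95% confidence intervals, beside the two-year figure. Define the time origin. The Background dates implementation to September 2010 in Ottawa and May 2013 in Saskatchewan, while the data windows open in January 2011 and January 2014. The same window year therefore begins about 4 months after implementation at one site and 8 months at the other.
2. Add time since implementation and its interaction with site to the model for receipt, keeping the random intercepts for provider.
3. Consider adding time to the exploratory outcome models as an inexpensive guard against possible drift.
4. In the Interventions paragraph, state whether the 80% rule is applied to men given the PtDA or to men using it, and over which period.

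**Cost.** No new patients are needed, and the dates are already required to place men in the window. The price is wider intervals per period than for the pooled figure, more so by quarter than by year. Linear time and its site interaction add two parameters to the combined model. There is less room in a Saskatchewan-only model, where the planned 90% leaves 400 × 0.10 = 40 men not given the PtDA. The trend is therefore better estimated in the combined model with the interaction.
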